### Secondary outcome measures

**Antibiotic requirements** will be measured by total number of completed days on oral and intravenous antibiotics.
**Protocol defined pulmonary exacerbations** will be recorded using the modified Fuchs criteria [18], which requires the presence of 4 or more of the following criteria:· Change in sputum· New or increased haemoptysis· Increased cough· Increased dyspnoea· Malaise, fatigue, or lethargy· Temperature above 38 °C· Anorexia or weight loss· Sinus pain or tenderness· Change in sinus discharge· Change in physical examination of the chest· Decrease in pulmonary function by 10%· Radiographic changes indicative of pulmonary infection

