**Methods:**

This randomised controlled mixed-methods trial aims to recruit 100 adults with CF cared for in one large regional CF centre. Participants are randomly allocated 1:1 to the intervention group (twice-weekly home monitoring of symptoms measured by the Cystic Fibrosis Respiratory Symptom Diary – Chronic Respiratory Infection Symptom Score (CFRSD-CRISS) and Forced Expiratory Volume in one second (FEV_1_)) or a control group (routine clinical care) for the 12-month study period. Measurements are recorded at study visits at baseline, 3, 6, 9 and 12 months. Spirometry, body weight, co-morbidities, medications, hospital inpatient days, courses of antibiotics (oral and intravenous), pulmonary exacerbations (defined by the modified Fuchs criteria) are recorded at each study visit. Health status, capability and health economics are measured at each study visit by the Hospital Anxiety and Depression Scale (HADS), the ICEpop CAPability measure for Adults (ICECAP-A), EuroQol 5 dimensions (EQ-5D-5L) questionnaire and an adapted resource use questionnaire. The patient experience is assessed by semi-structured qualitative interviews at baseline and 12 months.

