## Background

Cystic fibrosis (CF) is the most common fatal inherited condition in Caucasians, affecting more than 10,000 people in the UK [1] and at least 70,000 people worldwide [2]. CF is caused by abnormal function of the cystic fibrosis transmembrane conductance regulator (CFTR), a complex protein which functions primarily as a chloride channel, regulating movement of ions and fluid across epithelial surfaces [3]. CFTR dysfunction causes epithelial secretions to be abnormally dehydrated and viscous, resulting in damage to several organs including the lungs, pancreas, intestines and liver. Within the lungs, chronic infection and inflammation results in progressive lung disease and premature death due to respiratory failure. Survival in CF has dramatically improved over the last 40 years due to factors including improvements in antibiotic therapy, better nutrition and the development of centres devoted to the provision of specialised CF care. As a result, CF has changed from a predominantly paediatric disease to the current situation where the majority of individuals with CF survive into adulthood. The median predicted survival in the UK is currently in excess of 45 years of age [1] and that of people with CF born in the year 2000 is predicted to be in excess of 50 years of age [4].

People with CF often experience a burden of symptoms on a daily basis, typically including: cough, sputum production, wheeze, breathlessness, chest tightness and fever [5]. When patients develop worsening symptoms, they are advised to contact their CF multidisciplinary team (MDT) and may be diagnosed with a pulmonary exacerbation. Pulmonary exacerbations are typically treated with antibiotics targeted at the bacteria that cause chronic infection in that individual patient. However, symptoms of a pulmonary exacerbation do not usually develop suddenly, but instead worsen slowly over the course of several days to weeks. Patients presenting with less severe symptoms are more likely to receive a course of oral antibiotics, but as the exacerbation worsens the patient may require intravenous antibiotics. Intuitively, it would be expected that if the patient were diagnosed with a pulmonary exacerbation earlier, with milder symptoms, the requirement for intravenous antibiotics would be less.

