Anecdotally we know that some patients are able to perceive a change in their symptoms better than others. Some realise that they are developing an exacerbation early on, whereas others present when they have already become more severely unwell. Additionally, patients may know that they are developing an exacerbation, but are unable to come to clinic due to other commitments or due to a lack of clinic capacity. In either case, we suspect that if we were able to diagnose the exacerbation at an earlier stage we may be more likely to be able to treat it successfully with a course of oral antibiotics, rather than intravenous antibiotics. Additionally, in our experience if the patient is less unwell they are more likely to be able to receive intravenous antibiotics at home, rather than requiring admission. This could potentially be beneficial to the patient, preventing the complications of a more severe infection and could also reduce healthcare expenditure by averting a hospital admission.

Several previous studies have assessed the effect of telehealth or home monitoring in people with CF, but the vast majority of these studies have been small feasibility studies with limited external validity [6–13]. A randomised pilot study in CF patients demonstrated that home monitoring was able to detect more pulmonary exacerbations than standard care [14]. A large randomised controlled study of home monitoring is currently ongoing in the USA, assessing the primary outcome of change in forced expiratory volume in 1 s (FEV_1_) over a 12-month period [15]. Secondary outcome measures include the effect of home monitoring on CF respiratory symptom scores, pulmonary exacerbations, health-related quality of life, treatment burden, change in prevalence of resistant strains of bacteria and adverse events. There are no cost-effectiveness analyses included in this study and no qualitative assessment of the patient experience.

The primary aims of the current study are to (1) determine whether home monitoring is effective compared with routine care in reducing hospital inpatient bed days; and (2) assess whether this results in differences in health-related quality of life over a 12 months period in adults with CF. We hypothesise that participants randomly allocated to home monitoring will require fewer hospital inpatient bed days and that they will have better health-related quality of life compared with those receiving routine care.

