### Home monitoring group

Participants randomized to receive home monitoring will be provided with a Bluetooth-enabled digital spirometer and a ‘Microsoft Windows Mobile’ enabled mobile phone. Participants will be shown how to use the equipment before going home. Participants will be asked to record their FEV_1_ using a digital spirometer twice weekly (Monday and Thursday), which will take around 5 min to complete. Participants will also record their symptoms twice weekly (Monday and Thursday) on the mobile phone by completing the Cystic Fibrosis Respiratory Symptom Diary – Chronic Respiratory Infection Symptom Score (CFRSD-CRISS) [5]. This is a validated disease-specific tool (consisting of 16 questions) designed to detect symptoms of pulmonary exacerbations in CF, taking around 5 min to complete.

Data regarding lung function and symptoms will be automatically transmitted via a secure encrypted wireless connection and the research team will be able to access this data instantaneously on a specially designed website. The mean values of the first 2 weeks’ data will be used to determine the participants’ baseline levels for FEV_1_ and CFRSD-CRISS during the run-in phase. Following this initial 2-week period, the CF team will receive an email alert if participants’ FEV_1_ or symptoms deteriorate below a set threshold. The criteria that will trigger an email alert are one of: 1) a drop in FEV_1_ of 10% or more from baseline; 2) total score of the CFRSD-CRISS worsening by more than three points from baseline. Following an email alert, the CF team will contact the participant within 24 h to discuss their symptoms. Based on this discussion, the research team will advise the participant on the best management. If the participant needs to be assessed in the outpatient clinic, we will arrange the next available convenient appointment. Depending on the clinical assessment, participants will receive a course of antibiotics, either oral or intravenous depending on the severity of symptoms, sputum microbiology and patient choice. If prescribed antibiotics, we will document whether these were prescribed for a protocol-defined pulmonary exacerbation (see definition below).

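### Read plainly, antibiotic requirement pools oral and intravenous days, so it can hide, understate or reverse the intravenous-to-oral switch the trial expects; count the two routes separately

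*Protocol article*

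**What the plan says.** In the protocol article, the section Secondary outcome measures gives antibiotic requirements a single definition: the outcome "will be measured by total number of completed days on oral and intravenous antibiotics". Intravenous days and oral days are not named as outcomes in their own right there or elsewhere. Statistical and data analysis then has the listed outcomes summarised by group with 95% confidence intervals, with between-group tests described as exploratory.

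The Background says what home monitoring should change. If an exacerbation is diagnosed earlier, "with milder symptoms, the requirement for intravenous antibiotics would be less", and "we may be more likely to be able to treat it successfully with a course of oral antibiotics, rather than intravenous antibiotics". It adds a second effect: less unwell patients "they are more likely to be able to receive intravenous antibiotics at home, rather than requiring admission".

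Under Home monitoring group, antibiotics given after an alert and clinical assessment may be "either oral or intravenous depending on the severity of symptoms, sputum microbiology and patient choice". The abstract's Methods paragraph lists "courses of antibiotics (oral and intravenous") among the data recorded at each visit. Under Outcome measures, earlier intravenous courses are recorded at baseline as an item of their own.

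**The concern.** The trial expects a change in route, but this outcome, on its plain reading, adds the routes together. A patient whose intravenous course is replaced by an oral one has moved in the hoped-for direction, yet the total may stay the same, fall only a little, or rise. If alerts also lead to oral courses that would not otherwise have been given, the total goes up further. This is foreseeable: the Background cites a randomised pilot in which home monitoring detected more exacerbations than standard care.

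Inpatient bed days do not fill the gap. They fall when a patient is treated orally instead of being admitted, and also when intravenous treatment is given at home. Intravenous days separate the two, because they fall in the first case and not in the second. At stake is whether the trial can show its own mechanism, and whether a pooled figure is misread as no effect or as greater antibiotic need.

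**Working it through.** **Plan's own figures.** The protocol gives no figure for antibiotic days. Its one calculation, under Sample size, concerns inpatient days: 42 ± 1.96 × 10/√40 = 42 ± 3.1, or 38.9 to 45.1, and 36 ± 3.1, or 32.9 to 39.1. These match the printed (39, 45) and (33, 39), and nothing below affects them.

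**Algebra.** Per patient, let *s* be the number of courses switched from intravenous to oral, *L*iv and *L*o the course lengths in days, and *e* the extra oral courses prompted by alerts. Each course is taken to use one route only.

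- Change in intravenous days = −*s* × *L*iv
- Change in oral days = (*s* + *e*) × *L*o
- Change in pooled total = *s* × (*L*o − *L*iv) + *e* × *L*o

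With *L*o = *L*iv and *e* = 0 the pooled change is exactly zero, however many courses switch. With *L*o < *L*iv and *e* = 0 it is negative, but smaller than the fall in intravenous days. With *L*o > *L*iv, or with *L*o = *L*iv and *e* > 0, it is positive.

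**Illustration (all inputs assumed).** The control arm has 3 intravenous courses of 14 days, so 42 days. The share switched is 1/7, 0.30 or 0.50; the first equals 6/42, the relative reduction the protocol assumes for inpatient days. Oral courses last 10, 14 or 21 days. Extra oral courses are 0 or 0.5 per patient.

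One case in full: share 1/7 gives *s* = 3/7. Intravenous days change by −(3/7) × 14 = −6.0. Oral days change by (3/7) × 10 = +4.3, (3/7) × 14 = +6.0 or (3/7) × 21 = +9.0. The total changes by −1.7, 0.0 or +3.0. Half an extra oral course adds 5, 7 or 10.5 days, giving +3.3, +7.0 or +13.5.

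| Share switched | Change in intravenous days | Change in total, no extra courses (oral 10 / 14 / 21 days) | Change in total, 0.5 extra oral course (10 / 14 / 21 days) |
|---|---|---|---|
| 1/7 | −6.0 | −1.7 / 0.0 / +3.0 | +3.3 / +7.0 / +13.5 |
| 0.30 | −12.6 | −3.6 / 0.0 / +6.3 | +1.4 / +7.0 / +16.8 |
| 0.50 | −21.0 | −6.0 / 0.0 / +10.5 | −1.0 / +7.0 / +21.0 |

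In every cell the total falls by less than intravenous days do, does not move, or rises.

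**Setting.** Moving intravenous treatment from hospital to home changes neither intravenous nor oral days. It is therefore no evidence against pooling by route; its only relevance is that bed days cannot distinguish it from an oral switch.

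**The case against.** The strongest reply is that the definition names both routes and never says they are added, so it may mean a total for each. This stands as a possibility. Pooling is the more natural reading of one total covering both routes, but not the only one. It is also fair that an article leaves tabulation detail to a fuller document. What counts as the outcome is not tabulation detail, however, and the article fixes that itself.

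Second, extra oral courses are real antibiotic exposure, and a measure of antibiotic requirement ought to show them. That stands, and it is why the combined total is worth keeping. A reader might infer from a higher total that pooling alone creates the increase. It does not: at equal course lengths, all of any rise comes from added courses.

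Third, a reader might see a contradiction between courses in the abstract and days in the outcome section. The documents do not support that. The abstract lists what is recorded at visits; days can be derived from courses, and the abstract's stated aim uses the same label, antibiotic requirements.

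Fourth, a reader might assume that treatment setting, or the reason for an oral course, is already on record. The article names route; it does not say that home or hospital setting, or oral indication, is collected for each course.

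**Conclusion.** The point holds as a nearly free improvement to a secondary outcome. As plainly worded, the outcome is insensitive to the change of route that the Background expects, and it can move in the opposite direction to intravenous use.

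A reader might go further and say that pooling always cancels the switch. That is exact only when oral and intravenous courses have equal length and no oral courses are added. Otherwise the switch is partly offset or reversed. The actual size cannot be stated, because the protocol gives no course lengths, switch rates or extra-course rates; the table shows direction and range under assumed values only. The conclusion rests on the pooled reading. If a total for each route was meant, the same sentence still needs rewording to say so. The primary outcomes and the sample size are untouched, and the tests on this outcome are exploratory.

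**What to change.** Under Secondary outcome measures, replace the single definition with two outcomes: (1) completed days on intravenous antibiotics and (2) completed days on oral antibiotics. Summarise each by group with a 95% confidence interval. Keep the combined total as a descriptive addition, so that overall exposure is still visible.

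The cost is a change of wording. The present outcome already needs days from both routes, and the abstract names both routes in the recorded data; the only check is that each course's route is stored with its days. A further split of intravenous days into home and hospital, or of oral days by indication, is optional and should be added only if those items are collected. No treatment rule, visit or sample-size figure changes.

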**Spirometry (FEV**
_**1**_
**, FVC)** will be performed using a digital Vitalograph spirometer in the CF outpatient clinic in accordance with the American Thoracic Society guidelines [19]. The highest value for FEV_1_ and FVC obtained from three reproducible trials will be recorded and compared to predicted normal values.
**Body weight** (kg) will be measured using digital scales.
**Body mass index (BMI)** (kg/m^2^) will be measured using body weight and height recorded using a wall-mounted tape measure.
**Anxiety and depression** will be measured by the Hospital Anxiety and Depression Scale (HADS) [20]. This questionnaire is designed to detect and measure the severity of anxiety and depression. It consists of a series of 14 statements, with responses based on a 4-point Likert scale. The HADS is self-administered, with a higher score being indicative of greater anxiety or depression.
**Health economics analysis** will be conducted from a NHS and patient perspective. Participants will be asked to record any costs related to their care throughout the study, including the cost of visiting the hospital for outpatient visits (such as travel and parking costs) and loss of pay due to time off work. Participants will be asked to complete the EuroQol 5 dimensions (EQ-5D-5L), a generic health status questionnaire [21] and ICEpop CAPability measure for Adults (ICECAP-A), a generic measure of capability [22] at baseline, 3, 6, 9 and 12-month study visits. The researchers will record the costs associated with caring for each participant (such as costs of outpatient visits, inpatient admissions and staff time) and the cost of conducting the study (including staff costs and costs of the home monitoring equipment).

## Qualitative analysis

The qualitative aspects of the trial are a vital component in allowing us to better understand the context in which the trial takes place from the patient perspective. Participants will be invited to take part in semi-structured interviews at baseline and 12-months. These will help us to understand the reasons for patient participation, the contexts in which the trial takes place and will support interpretation of the findings (e.g. differential uptake or use of home-monitoring, reasons for patient withdrawal).

Topics of inquiry at baseline will include how individuals experience, understand and make decisions about their symptoms, health-care needs and service use. Participants’ expectations for home-monitoring will also be explored. Follow-up interviews will be undertaken with the intervention group to explore their experiences of using home-monitoring, including issues around acceptability and sustainability. This will include questions to explore the technical aspects of home-monitoring (e.g. ease of use), behavioural issues (e.g. perceived costs and benefits, necessary skill sets) and educational issues (e.g. adequacy of information and training). Suggestions for further improvement will also be sought. Where appropriate, follow-up interviews will examine reasons for study withdrawal.

### Statistical and data analysis

The outcomes listed will be summarized by group and 95% confidence intervals for these estimates will be calculated. Exploratory analyses will include basic tests to investigate differences between the intervention and control group, t-tests or chi-squared tests (or non-parametric alternative as appropriate). Cost-effectiveness will be assessed by calculating cost per reduction in hospital inpatient bed days and cost per quality-adjusted life year (QALYs) gained and appropriate sensitivity analyses will be conducted. Interview transcripts will be imported into NViVo and analysed using directed qualitative content analysis [23] to interpret meaning from the interview data in relation to the topics of inquiry, whilst allowing themes to emerge inductively from the data. To optimise rigour, data will be organized using the Framework method [24] and analysed as part of team approach, with an audit trail kept throughout. The qualitative and quantitative findings will be integrated using established methods [25] as part of the final analysis to allow us to interpret, understand and explain the trial findings.

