**Fig. 1 Fig1:**
[figure not shown]
Flow of patients through the study

Participants will be screened from the West Midlands Adult CF Centre database by the study investigators. If eligible, the study investigators will approach patients when they are attending routine clinic visits or during inpatient admissions to explain the study and if they are potentially interested they will be given the Participant Information Sheet. Having had time to consider the study and have any questions answered to their satisfaction, patients still keen to take part will be asked to provide written informed consent. It will be explained that they may withdraw from the study at any time.

At this point, baseline data will be obtained and the participant will be asked to take part in a semi-structured qualitative interview to assess the patient experience of their care to date and their expectations of participating in the study. Within strata, participants will then be randomly assigned to receive either home monitoring or routine care. The strata are based on the number of hospital admissions to receive intravenous antibiotics over the preceding 24 months, separated into four strata: ‘1–2 admissions’, ‘3–4 admissions’, ‘5–6 admissions’ and ‘more than seven admissions’. The randomisation will be completed by the selection of randomly ordered sealed opaque envelopes, with randomisation having been performed by a clerical member of the CF team with no knowledge of the study.

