## Outcome measures

All outcome measures will be recorded at baseline, 3, 6, 9 and 12 months, except for the semi-structured qualitative interview, which will be conducted at baseline and at 12 months (Fig. 1). Baseline data collection will include age, gender, weight (kg), body mass index (kg/m^2^), spirometry (FEV_1_, forced vital capacity (FVC)), concomitant medications, co-morbidities and health economic data. The number of courses of intravenous antibiotics and hospital admissions per year in the previous 2 years will also be recorded.

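### The only between-group tests named ignore the randomisation strata and baseline values, which loses precision that the design and the collected data could supply

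*Protocol article*

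**What the plan says.** Under Recruitment and randomisation, the article stratifies allocation: "Within strata, participants will then be randomly assigned to receive either home monitoring or routine care". On the factor it says: "The strata are based on the number of hospital admissions to receive intravenous antibiotics over the preceding 24 months". There are four bands. Of the mechanism it says: "The randomisation will be completed by the selection of randomly ordered sealed opaque envelopes". It does not mention blocks.

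Under Outcome measures, "All outcome measures will be recorded at baseline, 3, 6, 9 and 12 months", with an exception only for the interview. Baseline data also cover treatment history: "The number of courses of intravenous antibiotics and hospital admissions per year in the previous 2 years will also be recorded".

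Under Statistical and data analysis, the intervals promised are for each arm separately: "The outcomes listed will be summarized by group and 95% confidence intervals for these estimates will be calculated". Comparison between arms follows as a second step: "Exploratory analyses will include basic tests to investigate differences between the intervention and control group". The methods given are "t-tests or chi-squared tests (or non-parametric alternative as appropriate". Neither the strata nor the baseline values appear in any comparison in the article.

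**The concern.** The stratification factor is the recent history of what one of the two primary outcomes measures, so it was presumably chosen because it predicts bed days. A two-sample t-test leaves the variation between strata in its standard error. The same holds for CFQ-R, the other primary outcome: a patient's baseline score usually explains much of the later score, and a plain comparison of 12-month values makes no use of it.

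At stake is the precision of the treatment comparison in a trial planned on 40 evaluable patients per arm. The article states comparative primary aims and a directional hypothesis, so the width of the between-arm interval matters even though the tests are called exploratory.

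**Working it through.** **Inputs from the article (Sample size):** mean bed days 42 and 36 (difference 6), SD 10, 40 patients per arm, 100 recruited to allow for drop-out.

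**Assumed here:** a correlation R of 0.3 or 0.5 between stratum and 12-month bed days, and a two-sided 5% level. The article gives neither.

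**1. The plan's own figures reproduce.** Per-arm half-width = 1.96 × 10/√40 = 3.10. This gives (38.9, 45.1) and (32.9, 39.1), which round to the printed (39, 45) and (33, 39). Also 80/(1 − 0.20) = 100. These per-arm intervals are correct and are not the problem.

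**2. Unadjusted difference between arms.** Half-width = 1.96 × 10 × √(2/40) = 4.38 days.

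**3. Difference adjusted for stratum (linear model).** The residual SD is 10 × √(1 − R²), so the half-width is 4.38 × √(1 − R²). The number of patients that an unadjusted analysis would need for the same width is 80/(1 − R²).

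| R | √(1 − R²) | Half-width (days) | Narrowing | Equivalent evaluable N |
|---|---|---|---|---|
| 0 | 1.000 | 4.38 | – | 80 |
| 0.3 | 0.954 | 4.18 | 5% | 88 |
| 0.5 | 0.866 | 3.80 | 13% | 107 |

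For a 6-day difference, normal-approximation power is 76.5% unadjusted, and 80.3% or 87.3% adjusted at R = 0.3 or 0.5.

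**4. Calibration of the t-test.** If the strata are balanced by design, the true standard error is smaller than the t-test's by the factor √(1 − R²). The actual type I error is then 2 × [1 − Φ(1.96/√(1 − R²))]:
- R = 0.3: 2 × [1 − Φ(2.055)] = 4.0%
- R = 0.5: 2 × [1 − Φ(2.263)] = 2.4%

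**5. Check by simulation.** Each setting had 6,000 trials of 80 patients with normal outcomes and assumed stratum shares of 50/25/15/10%. Allocation was either in permuted blocks of 4 within strata or by unblocked 1:1 randomisation. Type I errors are from runs with no true difference.

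| Allocation | R | t-test type I error | t-test half-width | Adjusted half-width |
|---|---|---|---|---|
| Blocked | 0.3 | 3.8% | 4.44 | 4.24 |
| Blocked | 0.5 | 2.5% | 4.45 | 3.86 |
| Unblocked | 0.3 | 5.1% | 4.48 | 4.36 |
| Unblocked | 0.5 | 5.2% | 4.47 | 3.95 |

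The adjusted model's type I error was 4.9% to 5.1% in these four settings. Adjustment is more precise in all four. The t-test is conservative only in the blocked ones.

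**6. CFQ-R.** Let r be the correlation of the baseline with the 12-month score (0.5 to 0.7 assumed).
- Against a t-test on final values, ANCOVA has variance factor 1 − r², a saving of 25% at r = 0.5 and 49% at r = 0.7.
- Against a t-test on changes from baseline, with equal variances, the ratio is (1 − r²)/[2(1 − r)] = (1 + r)/2, a saving of 25% at r = 0.5 and 15% at r = 0.7.

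The article does not say which form the t-test would take.

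**The case against.** The strongest reply is that this is mostly silence. The article is condensed, an unseen SAP could add a model, the list of tests is worded as non-exhaustive, and the tests are exploratory in a trial titled a pilot and sized on precision without a power claim. Much of this stands, and it limits the weight of the point. It does not remove the point, because the article does more than stay silent: it names methods, and t-tests, chi-squared tests and their usual rank alternatives are unadjusted by construction.

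A reader might also infer more than the article supports:

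- **That the t-test's error rate is below 5% and its intervals too wide.** This needs balance enforced within strata. Randomly ordered envelopes do not establish that. Without blocking the t-test is valid, only less precise. Nor can this conservatism and chance imbalance in the stratum factor both be charged: the first needs balanced strata, the second unbalanced ones.
- **That the confidence intervals promised in the plan are too wide.** Those intervals are group summaries. No between-arm interval is specified, so the comparison in step 2 is with the interval that an unadjusted t-test would imply.
- **That early leavers will bias the bed-day comparison.** The article does not say whether truncated counts, completers or person-time would be analysed, so no bias can be shown.
- **That a count model is required.** A t-test does estimate a difference in mean days, and a negative binomial model is one option among several. The gains in step 3 are for a linear model; none was calculated for a count model.

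The size of the gain is also assumed. At R = 0.3 it is modest.

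**Conclusion.** The point holds as a loss of precision. The between-group tests named make no use of a stratification factor built into the randomisation, or of baseline values that are already collected. For bed days, the implied between-arm interval is about 5% to 13% wider than need be in terms of its own width (4.38 days against 4.18 or 3.80), equivalent to about 88 or 107 evaluable patients instead of 80. For CFQ-R the saving in variance is about 15% to 49%, depending on r and on whether final or change scores would be tested.

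These sizes rest on assumed correlations, on the protocol's SD of 10 and 40 per arm, and on a linear model. The loss arises with or without blocking. The consequence is wider intervals and lower power in exploratory tests, not false positives, so this is a moderate improvement to the analysis and does not threaten the trial's validity.

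**What to change.** 1. **Bed days:** report the between-arm difference in mean days with a 95% CI from a model that includes the prior-admission stratum or the 24-month admission count. Two suitable choices are a linear model with robust standard errors, or a count model with log follow-up time as offset. If a count model is used, convert its rate ratio to an adjusted difference in mean days, which the planned cost per bed day averted also needs. State that the offset assumes drop-out is unrelated to later bed use.
2. **CFQ-R and the other continuous outcomes:** use ANCOVA or a repeated-measures mixed model, adjusted for the baseline value and the stratum.
3. **Unadjusted tests:** keep them as sensitivity analyses.
4. **Allocation:** state whether it was blocked within strata, since that decides whether the unadjusted tests are conservative or correctly calibrated.

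The cost is some analysis wording, a few lines of code and a few degrees of freedom (three for four strata, 78 to 75 at 80 patients). The article already provides for collecting the strata and baseline values.
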